## Interventions

### Explanation for the choice of comparators {6b}

The SOUL study is a pragmatic comparison between two existing management strategies that are both widely considered routine standard clinical care. All potential participants are planning to undergo ureteroscopy with a urologist trained in ureteroscopy in accordance with American Urological Association (AUA) guidelines. The intervention in this trial is stent omission. Patients will either continue to receive a ureteral stent with the surgeon’s choice of stent, or undergo stent omission, both of which are widely accepted as standard clinical care. In the observational cohort, assignment to stent omission will be at the discretion of the operating urologist per routine clinical practice, which may or may not include patient preferences. In the randomization cohort, assignment to stent omission versus stent placement will be by 1:1 randomization. When a stent is placed, it may or may not be left on a string (tether), at the operating urologist’s discretion. The duration of stenting, and how it is removed, is left to the discretion of the urologist.

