Approximately 85% (449) of the observational cohort consented patients are expected to undergo an eligible ureteroscopy. From our prior data, approximately 70% (314) of these patients will receive a stent during ureteroscopy, and 135 (30%) will have stent omission. Assuming a 10% loss-to-follow-up (days 7–10 pain interference questionnaire not completed), this will result in 283 stent placement patients and 121 stent omission patients evaluable for the primary analysis of the observational cohort. Assuming a two-sided 2.5% type I error for each primary endpoint, 283 patients in the stent placement arm and 121 patients in the stent omission arm will provide 99.1% power to detect a clinically meaningful difference of 5 points between treatment arms for the change from pre-surgery in PROMIS® pain interference measure at days 7–10, assuming a standard deviation of 10 using a two-sample *t*-test. Sensitivity to the stented proportion and proportion agreeing to randomization (Table 2) demonstrates at least 84% power to detect a clinically significant difference in pain interference.

**Table 2 Tab2:** Observational cohort power with sensitivity to our assumptions

Proportion agrees to randomization (total approached)	Proportion stented	Sample size total (stented:stent omission)	Power
33% (792)	70%	404 (121:283)	99.1%
	50%	404 (202:202)	99.7%
	25%	404 (101:303)	99.1%
50% (528)	70%	202 (141:61)	84.2%
	50%	202 (101:101)	90.0%
	25%	202 (51:151)	86.7%

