The power estimates presented assume that each observation is independent. However, due to surgeon preference in the observational cohort, there may be a potential for clustering which could impact the power of the study. We expect that surgeons within a site may behave more similarly and the variability between sites will be the correlation that will be important. The intraclass correlation (ICC) across multiple studies and therapeutic areas has been shown to likely be small, with a range between 0.01 and 0.05 [31]. Using our planned sample sizes, we can estimate the sample size needed under a range of ICCs using a method described by Klar and Donner [32] with an estimate of the sample size inflation factor (IF) based upon the ICC and the average sample size per cluster. Table 3 provides the power from using the effective sample size and the assumed proportions for each arm (stent vs stent omission using standard power calculations for the two-arm mean difference using a *t*-test with a two-sided type I error of 0.025 with the assumptions used for Pain Interference described above.

**Table 3 Tab3:** Power for pain interference co-primary endpoint in observational cohort with clustering effect (ICC), assuming 14 participating sites

Proportion agrees to randomization	Total approached	Final observational cohort sample size	Proportion stented	ICC group			
				**0**	**0.01**	**0.02**	**0.05**
33%	792	404	70%	99.1%	96.5%	92.3%	76.3%
			50%	99.7%	98.6%	96.1%	83.7%
			25%	99.1%	94.4%	89.0%	71.0%
50%	528	202	70%	84.2%	78.6%	73.4%	59.6%
			50%	90.0%	85.8%	81.2%	68.0%
			25%	86.7%	73.5%	68.0%	54.2%

For the co-primary endpoint of healthcare utilization in the observation cohort, if we assume that the stented proportion is 50%, with 202 participants per treatment group and a two-sided 2.5% type I error (alpha), we have 90% power to detect a treatment effect, marginal probabilistic index, of 60.1%. If the stented proportion is as low as 25% or as great as 75%, then we can infer that with 90% power, we will be able to detect a treatment effect between 60.1% and 64.3% as the sample size will be at least 101 per stent group.

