### Interim analyses {21b}

An interim analysis after 396 patients are accrued is planned for confirmation of assumptions and re-estimation of sample size and power. Measures to be assessed include the proportion of patients who agree to join the randomization trial arm, the overall standard deviation of the primary endpoint, pain interference at days 7–10 change from pre-surgery, the proportion stented in the observational arm, and the intraclass correlation (ICC) in the observational arm. The sample size and power of each trial cohort will be reassessed based upon the interim analysis estimates compared to the assumed estimates. The results will be shared with the trial team and discussed with the funder.

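### Table 3's clustered powers use an inflation factor that fits only sites stenting all or none of their patients, although both arms can occur within a site in the observational cohort

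*Protocol article*

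**What the plan says.** All places are in the protocol article.

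- **Sample size {14}, base case.** The observational cohort is expected to yield "283 stent placement patients and 121 stent omission patients evaluable for the primary analysis of the observational cohort", which is stated to give "99.1% power to detect a clinically meaningful difference of 5 points between treatment arms", "assuming a standard deviation of 10 using a two-sample" t-test. The 10% loss to follow-up is already taken off these counts.
- **Sample size {14}, clustering.** Surgeon preference is named as a possible source of clustering, and surgeons within a site are expected to act alike to some degree. The ICC is taken as 0.01 to 0.05. The sample is shrunk using "an estimate of the sample size inflation factor (IF) based upon the ICC and the average sample size per cluster", and power is then read from an ordinary t-test with a "two-sided type I error of 0.025". Table 3 shows the result for 14 sites. For 404 patients with 70% stented it prints 99.1, 96.5, 92.3 and 76.3% at ICC 0, 0.01, 0.02 and 0.05.
- **Explanation for the choice of comparators {6b}.** In this cohort, "assignment to stent omission will be at the discretion of the operating urologist per routine clinical practice".
- **Observational cohort analysis (pain interference).** Random effects for physician or practice are considered only if further imbalance is seen.
- **Interim analyses {21b}.** The ICC and the proportion stented in the observational arm are re-estimated, and "The sample size and power of each trial cohort will be reassessed based upon the interim analysis estimates compared to the assumed estimates".

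**The concern.** The factor 1 + (m − 1) × ICC is the design effect of a cluster-randomised trial, where everyone at a site gets the same treatment and the whole site effect falls on one arm. When both treatments occur at a site, much of the site effect is shared by the arms and cancels from the difference. How much cancels depends on how unevenly stent use is spread over sites. Table 3 has no term for this, so it implicitly assumes the extreme case.

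Pain interference is a co-primary endpoint, and Table 3 is the only power statement for it in this cohort that allows for clustering. The interim review re-estimates the ICC. If the same factor were used there, an ICC of 0.05 would read as about 76% power whether stent rates were nearly equal across sites or very different.

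**Working it through.** **Inputs from Sample size {14}.** Difference 5, SD 10, two-sided alpha 0.025, N = 404 or 202, 70% stented, 14 sites, ICC 0.01 to 0.05. Mean cluster size m = 404/14 = 28.86 or 202/14 = 14.43.

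**Assumed input.** rho_x is the share of the variance in stent use that lies between sites: 0 means the same stent rate everywhere, 1 means each site stents all or none. It is not in the document, so 0.1 to 0.5 is shown. At a mean of 70%, the SD of site stent rates is √(rho_x × 0.7 × 0.3), about 14, 25 and 32 percentage points at rho_x 0.1, 0.3 and 0.5.

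**Step 1. Reproduce the printed figures.** IF = 1 + (m − 1) × ICC, effective N = N/IF split 70:30, power from the noncentral t.

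| N | ICC | IF | Effective N | Recomputed | Printed |
|---|---|---|---|---|---|
| 404 | 0.01 | 1.279 | 316.0 | 96.5% | 96.5% |
| 404 | 0.02 | 1.557 | 259.4 | 92.4% | 92.3% |
| 404 | 0.05 | 2.393 | 168.8 | 76.2% | 76.3% |
| 202 | 0.01 | 1.134 | 178.1 | 78.7% | 78.6% |
| 202 | 0.02 | 1.269 | 159.2 | 73.5% | 73.4% |
| 202 | 0.05 | 1.671 | 120.9 | 59.9% | 59.6% |

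All 18 cells with ICC above 0 agree within 0.5 points, so the method is established.

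**Step 2. No site effects in the model.** The variance of the arm difference is SD² × (1/n1 + 1/n0) × [1 + (m − 1) × ICC × rho_x]. This equals the plan's factor only at rho_x = 1. Example: N = 404, ICC 0.05, rho_x 0.3 gives 1 + 27.86 × 0.05 × 0.3 = 1.418, effective N 404/1.418 = 284.9, power 94.6%.

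| N, ICC | Printed | rho_x 0.1 | rho_x 0.3 | rho_x 0.5 |
|---|---|---|---|---|
| 404, 0.05 | 76.3% | 98.0% | 94.6% | 89.9% |
| 404, 0.01 | 96.5% | 98.9% | 98.5% | 98.0% |
| 202, 0.05 | 59.6% | 81.3% | 76.0% | 71.0% |
| 202, 0.01 | 78.6% | 83.5% | 82.4% | 81.3% |

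Here the printed powers are too low: by about 11 to 22 points in the ICC 0.05 rows shown, and by about 2 points at 404 patients and ICC 0.01.

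**Step 3. Site as fixed effects.** Only within-site contrasts remain, and the factor is approximately (1 − ICC)/(1 − rho_x).

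- N = 404, ICC 0.05, rho_x 0.5: 0.95/0.5 = 1.90, power about 86% by formula. Simulation with 14 sites and beta-distributed site stent rates gives about 82%. Printed: 76.3%.
- N = 202, ICC 0.05, rho_x 0.5: the same factor gives about 54% by formula and about 50% simulated. Printed: 59.6%.
- N = 202, ICC 0.01, rho_x 0.3: 0.99/0.7 = 1.414, about 68% by formula. Printed: 78.6%.

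The formula is optimistic when rho_x is high. At 202 patients the printed powers can therefore be too high.

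**Step 4. Site as a random intercept.** Simulating N = 202, ICC 0.05, rho_x 0.5 with the ICC treated as known and site effects unrelated to site stent rates gives about 74%. The reversal in step 3 thus belongs to fixed site effects.

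**The case against.** **The calculation is not faulty.** The method is stated openly and its ICC-above-0 cells reproduce. That stands: the issue is the choice of design effect.

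**Some clustering of stent use is anticipated, so a cautious bound is reasonable.** This stands in part. A reader might infer that stenting is decided independently patient by patient, so that the ICC is irrelevant. The text does not support that: it leaves the choice to the urologist and expects similarity within sites. But similarity is not all-or-none. Nor is the table a bound under every model, as the fixed-effects cases at 202 patients show. Against this, the protocol mentions only random effects, and only conditionally. In the one random-intercept case checked, the printed figure was still too low.

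**The size rests on an unknown, and the large gaps occur at the top of the ICC range.** Correct. Unequal site sizes matter too. With an assumed coefficient of variation of 0.8, the effective m is 28.86 × 1.64 ≈ 47; at ICC 0.05 and rho_x 0.3 the factor is about 1.69 and power about 90% rather than 94.6%. Table 3 also ignores unequal sizes, so this does not rescue its figures.

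**Nothing depends on the table.** A reader might infer that Table 3 sized the cohort, or that the interim will lead to a needless enlargement. Neither is supported. The cohort size comes from the assumption that one third of patients accept randomization. The interim section gives no formula, threshold or enlargement rule, so a misjudgement there follows only if the same factor is reused.

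**Conclusion.** The point holds in limited form. Table 3's clustered columns describe sites that stent all or none of their patients, which is not how treatment is chosen in this cohort.

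- **Without site effects,** power is understated. The gap is about 14 to 22 points at 404 patients, 70% stented and ICC 0.05 for rho_x 0.5 down to 0.1, and about 2 points at ICC 0.01.
- **With fixed site effects and strongly clustered stent use,** power can be overstated, by about 10 points at 202 patients, ICC 0.05 and rho_x 0.5.

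These sizes assume 14 sites of equal size, no clustering by surgeon within site, and values of rho_x that the document does not supply. The cohort size and the primary analysis are untouched. What is wrong is the stated power of a co-primary endpoint under clustering, and the interim list omits the quantity that determines how much the ICC matters.

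**What to change.** 1. In Sample size {14} and Table 3, restate the clustered powers with a factor that includes between-site variation in stent use and matches the model to be fitted. Without site effects, use 1 + (m − 1) × ICC × rho_x. With site effects, use simulation; for fixed effects, (1 − ICC)/(1 − rho_x) serves as an approximation, marked as optimistic at high rho_x.
2. Show a range of rho_x, for example 0.1 to 0.5. The collaborative's registry could inform it from stent rates by practice.
3. If the present columns are kept, label them as the rho_x = 1 limit for the contrast without site effects.
4. In Interim analyses {21b}, add the between-site variation in stent use to the measures and use it together with the ICC when the observational cohort's power is reassessed.

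The cost is one recalculated table and one interim quantity obtained from site and stent status, which are already collected. No extra patients are needed. The downside is that the table gains a dimension and some entries become less favourable.

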### Recruitment {15}

To date, ten practices in Michigan who are members of MUSIC are taking part in the SOUL trial. In aggregate, these practices perform 2878 ureteroscopies annually, with an estimated 1960 meeting study eligibility criteria. MUSIC is also currently undergoing an expansion of membership to include practices outside Michigan and thus far four such practices have indicated their intention to participate in the SOUL study. These “Outdoor MUSIC” sites perform an estimated additional 1300 ureteroscopies annually, of which at least half are estimated to meet SOUL eligibility criteria.

## Assignment of interventions: allocation

### Sequence generation {16a}

Participants in the randomization cohort will be randomized intraoperatively using an online computer-based system (https://randomize.net/) to either stent omission or stent placement in a 1:1 ratio. This will take place after the completion of the lithotripsy portion of the procedure and verification of second-stage eligibility by the operating urologist. Blocked, stratified randomization based upon surgeon-classified stone location (renal only versus ureteral with or without renal), with random block sizes will be used to ensure group balance.

### Concealment mechanism {16b}

Surgeons will not perform intraoperative randomization on the web-based platform until they have completed the lithotripsy portion of the procedure and verified that the participant meets second-stage eligibility criteria. Thus, randomized allocation does not occur until the point of performing the assigned intervention.

### Implementation {16c}

The trial has a dedicated biostatistician who has programmed online randomization platform with the trial design and the online platform generated the allocation sequence to be implemented. The randomization of individual participants and assignment to intervention will occur intraoperatively, only after completion of the lithotripsy portion of the procedure and confirmation by the operating urologist that the participant meets second-stage eligibility.

## Assignment of interventions: blinding

### Who will be blinded {17a}

The operating urologist will need to perform the allocated treatment (stent omission or stent placement) and therefore cannot be blinded. Because the presence of a stent necessitates arrangements need to be made for future stent removal, patients will also be informed of the presence or absence of a stent immediately following their surgery and will not be blinded.

### Procedure for unblinding if needed {17b}

Not applicable. Neither urologists nor patients will be blinded.

## Data collection and management

### Plans for assessment and collection of outcomes {18a}

Participating MUSIC practices submit data to a web-based clinical registry maintained by the MUSIC coordinating center developed in conjunction with a vendor (ArborMetrix, Ann Arbor, Michigan). The registry includes approximately 150 unique variables with information on patient demographics; laboratory, imaging results; comorbid conditions; treatments; and patient outcomes including complications and mortality, among others. Data collection is guided by standard variable definitions and collaborative-wide operating procedures. In terms of quality assurance, members of the coordinating center conduct on-site audits to ensure the appropriate identification of cases and the integrity of data entered into the registry.

All participants in both the randomization and observational cohorts will receive PRO questionnaires via e-mail or alternative means of communication at several prespecified time points: pre-operatively, at 7–10 days after surgery, and at 4–6 weeks after surgery. If the patient is unable to complete the study questionnaires electronically, the patient may complete questionnaires over the telephone with assistance from a SOUL study team member or paper questionnaires upon request. Patients will also receive automated questionnaires (Daily Ecological Momentary Assessments, EMA) via text message, daily for 10 days after surgery and on day 30 after surgery. PRO and EMA responses will be recorded and secured.

### Plans to promote participant retention and complete follow-up {18b}

Participation in the SOUL study is short-term, and minimal loss to follow-up is expected. Follow-up is limited to only routine postoperative clinical care, and no study-specific visits or tests are required.

Patients will receive PRO surveys electronically via an automated system. If a patient does not log-in or fails to complete the preoperative PRO survey, they will receive an electronic automated reminder and will be contacted by the MUSIC Coordinating Center. If a patient does not log-in or fails to complete the 7-day survey, they will receive an electronic automated reminder and will be contacted by the MUSIC Coordinating Center to facilitate its completion by the end of post-operative day 10. The SOUL Study Team may also administer the PRO questionnaires via REDCap, phone, or paper if the participant is unable to complete surveys through the MUSIC Registry. Similar procedures will be used for the completion of the 4–6-week PRO surveys.

### Data management {19}

Study participant research data, which is for purposes of statistical analysis and scientific reporting, will be transmitted to and stored at ArborMetrix. The study data entry and study management systems used by clinical sites and by MUSIC research staff will be secured and password protected. Data are regularly audited by manual review for quality and fidelity as part of routine MUSIC operating procedures. At the end of the study, all study databases will be de-identified and archived at MUSIC.

### Confidentiality {27}

Participant confidentiality and privacy is strictly held in trust by the participating investigators, their staff, and the study coordinating center. Therefore, the study protocol, documentation, data, and all other information generated will be held in strict confidence.

All research activities will be conducted in as private a setting as possible.

The MUSIC coordinating center and duly authorized representatives, representatives of the Institutional Review Board (IRB), or regulatory agencies may inspect all documents and records required to be maintained by the investigator, including but not limited to medical records (office, clinic, or hospital) and pharmacy records for the participants in this study. The clinical study site will permit access to such records.

The study participant’s contact information will be securely stored at each clinical site for internal use during the study. At the end of the study, all records will continue to be kept in a secure location for as long a period as dictated by the reviewing IRB, Institutional policies, or PCORI requirements.

### Plans for collection, laboratory evaluation and storage of biological specimens for genetic or molecular analysis in this trial/future use {33}

Not applicable. No biological specimens will be collected.

## Statistical methods

### Statistical methods for primary and secondary outcomes {20a}

Co-primary outcome: postoperative days 7–10 PROMIS® Pain Interference change from pre-surgery.

#### Randomized cohort analysis

A linear (ANCOVA) model will be used on the intention to treat (ITT) population to compare the two treatments, with PROMIS Pain Interference *t*-score at postoperative days 7–10 as the dependent variable and treatment group, stratification factor (stone location [kidney or ureter]) and pre-surgery (baseline) Pain Interference *t*-score as the independent variables [33]. The adjusted parameter estimate for treatment group (stent omission vs. placement) will be reported with the associated 97.5% CI and *p*-value (based on a type 3 *F*-test) that allows testing the hypothesis that Pain Interference differs between the two treatment groups. Multiple imputation will be used to address missing data and will be described fully in the statistical analysis plan. Sensitivity analysis will be conducted with the same analysis in the pain-modified intent-to-treat (PmITT, see Sect. 20c) population to assess the robustness of the effect found in the primary analysis. Additional sensitivity analysis will be conducted if there is baseline imbalance.

#### Observational cohort analysis

The primary analysis for the observational study will be similar to the model described in the randomized cohort except additional independent patient and surgical baseline covariates (age, sex, body mass index (BMI), Charlson comorbidity index, pre-surgery depression t-score, pre-surgery anxiety *t*-score, narcotic use, stone location (kidney or ureter), and stone size) will be included in the model to adjust for potential confounders that are more likely to be unbalanced between the treatment groups owing to lack of randomization. Additionally, a multivariable model with random effects for physician or practice will be considered if there is further imbalance in these factors.

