## Methods: participants, interventions, and outcomes

### Study setting {9}

Participants will be enrolled at multiple urology practices that are part of MUSIC, consisting of various sizes and practice settings (academic centers, community hospitals, private provider groups) throughout the USA. The current list of participating sites can be found on ClinicalTrials.gov. We anticipate 14 centers throughout the country.

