#### Observational cohort analysis

The same general approach used in the RCT will be applied to the observational study with the healthcare utilization rank for each patient and the rules for comparing pairs of patients between arms. However, to address possible clustering among surgeons and sites while protecting unbiasedness of treatment effects and to preserve power, the analysis approach of Dong et al. [36] will be implemented. Specifically, this approach incorporates the notion of risk-matching by forming strata according to risk groups (as described by Pocock et al. [29]) without resulting in loss of information by losing matched pairs when there is an imbalance in sample size between groups. The stratified approach uses the unmatched method to calculate the win ratio statistics within stratum, thus providing an intermediate position between the matched pairs approach and the unmatched approach. Specifically, we will include site in the determination of risk strata. To form risk group strata, the outcome of healthcare utilization categorized as yes versus no will be modeled using a logistic model with fixed effects including baseline variables: site, stone location (kidney only vs ureter), stone size, and Charlson comorbidity score. A risk score for each patient will be obtained using the logistic model’s coefficients. Stratification will be performed based upon risk score. Risk score groups will be defined using natural bins (if they are apparent) or percentiles. Then, within each stratum, an unmatched approach will be used to calculate the win ratio. The overall win ratio will be estimated using the Mantel–Haenszel-type weight and reported with a 97.5% confidence interval. The method for adjustment will be described in detail in the SAP and finalized prior to data lock. Sensitivity analysis will be conducted with the same analysis in the HCUmITT population to assess the robustness of the effect found in the primary analysis.

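### The primary observational pain model has no site term unless an undefined imbalance appears, although the plan itself discounts power for clustering by site

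*Protocol article*

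**What the plan says.** All references are to the Protocol article.

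- **Observational cohort analysis, pain interference.** The primary model follows the randomized-cohort ANCOVA (treatment, stone location, baseline score) and adds "additional independent patient and surgical baseline covariates (age, sex, body mass index (BMI), Charlson comorbidity index, pre-surgery depression t-score, pre-surgery anxiety" score, narcotic use, stone location and stone size. Neither site nor surgeon is listed. Then: "a multivariable model with random effects for physician or practice will be considered if there is further imbalance in these factors".
- **Sample size {14}.** On the same endpoint and cohort: "due to surgeon preference in the observational cohort, there may be a potential for clustering which could impact the power of the study". On the level of clustering: "We expect that surgeons within a site may behave more similarly and the variability between sites will be the correlation that will be important". The ICC is taken as small, "with a range between 0.01 and 0.05", and Table 3 gives the power at 0, 0.01, 0.02 and 0.05 with 14 sites.
- **Observational cohort analysis, unplanned healthcare utilization.** Site enters the risk strata, and the stated purpose of the stratified approach is "to address possible clustering among surgeons and sites while protecting unbiasedness of treatment effects and to preserve power".
- **Explanation for the choice of comparators {6b}.** In this cohort the operating urologist decides whether to stent.
- **Interim analyses {21b}.** The ICC is estimated at the interim, but only to reassess sample size and power.

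**The concern.** The plan allows for site clustering when it computes power for this endpoint, then states a primary model in which patients are independent given the patient-level covariates. It also treats the two co-primary endpoints of one cohort differently in this respect.

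The route by which site could enter is loose in three ways. The random-effects model is only to be considered, no degree of imbalance is named, and it is unclear whether the factors in question are the patient covariates or physician and practice. The choice of primary model can therefore be made after the data are seen.

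Two things are at stake. The first is precision: if outcomes correlate within site and stent use also differs by site, the standard error is understated and the test rejects too often. The second is confounding: if sites that stent more also have systematically higher or lower pain scores, the site difference is read as a stent effect.

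**Working it through.** **Inputs from the protocol.** 283 stented and 121 stent-omission patients evaluable (404 in total); target difference 5 points; SD 10; two-sided alpha 2.5%; ICC 0.01 to 0.05; number of sites: "We anticipate 14 centers throughout the country". Average patients per site: 404/14 = 28.86.

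**Step 1: reproduce Table 3 (404 patients, 70% stented).** Design effect DE = 1 + (28.86 − 1) × ICC. Effective sample size = 404/DE, split 70:30, entered into a two-sample t-test power calculation.

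| ICC | DE | Effective N | Power computed | Power stated |
|---|---|---|---|---|
| 0 | 1.000 | 404.0 | 99.1% | 99.1% |
| 0.01 | 1.279 | 316.0 | 96.5% | 96.5% |
| 0.02 | 1.557 | 259.4 | 92.4% | 92.3% |
| 0.05 | 2.393 | 168.8 | 76.2% | 76.3% |

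The table reproduces. The power section therefore uses a design effect of up to 2.39, while the stated primary model implicitly uses 1.

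**Step 2: cost of ignoring that design effect.** This DE applies when every patient at a site gets the same treatment, so it marks the extreme case. The true standard error is √DE times the model's, and the actual type I error is 2 × [1 − Φ(2.241/√DE)].

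- ICC 0.01: √1.279 = 1.13; error 4.7%.
- ICC 0.02: √1.557 = 1.25; error 7.2%.
- ICC 0.05: √2.393 = 1.55; 2.241/1.547 = 1.449; error 14.7%.

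**Step 3: stenting that varies only partly by site.** The protocol gives no between-site spread in stenting, so it has to be assumed. Simulations used 404 patients, 14 sites and no true effect. Site outcome levels were unrelated to site stenting rates.

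| Assumed spread in stenting | ICC 0.01 | ICC 0.02 | ICC 0.05 |
|---|---|---|---|
| None | 2.6% | 2.5% | 2.5% |
| Between-site ICC of stenting 0.1 | 2.9% | 2.7% | 3.8% |
| Between-site ICC of stenting 0.3 | 3.0% | 3.8% | 5.8% |
| Between-site ICC of stenting 0.6 | 4.0% | 4.9% | 9.8% |
| Logit SD 1 to 2 | 3.1–3.6% | 3.2–4.1% | 4.4–6.9% |

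These runs compared the arms without covariates. A further check that adjusted for the baseline score gave about 2.8% to 8.1% without site. In the 0.3 row at ICC 0.05, the estimates had an empirical SE of 1.30 against an average model SE of 1.10, a ratio of 1.30/1.10 = 1.18.

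**Step 4: site stenting rate and site outcome level correlated.** With an assumed correlation of 0.5 and a between-site ICC of stenting of 0.3, the bias was 0.5, 0.7 and 1.2 points at ICC 0.01, 0.02 and 0.05. Type I error was 4.9%, 8.0% and 18.0%. The largest of these biases is 1.2/5 = 24% of the target difference. The baseline-adjusted check reached 24% type I error at a correlation of 0.5.

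**Step 5: site as a fixed effect.** Across all these simulations the error stayed at about 2% to 3% (1.9% to 3.1%), including the correlated settings.

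**The case against.** The strongest defence has four parts.

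*The trigger may be apt.* If the imbalance meant is of physician or practice between arms, it describes stent use that differs by site. That is half of the condition under which omitting site does harm, and with no such difference omission costs nothing (Step 3, first row). So the trigger cannot be called wrong in kind. It is still optional and without a threshold, and its meaning is ambiguous.

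*The harm is conditional.* A reader might infer that the plan expects clustering and that its interval is certainly too narrow. The documents speak of clustering only as possible and give no between-site spread in stenting. At ICC 0.01 to 0.02 with moderate spread, the excess over 2.5% is small. The 14.7% is an extreme, not a forecast: it needs stenting wholly determined by site, and a site fixed-effects model could not then estimate the treatment effect at all. The simulations also leave out the nine added covariates, which could absorb some between-site variation.

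*Detail may sit in the analysis plan.* That would answer a silence. Here the protocol states the primary model, its covariates and a discretionary condition.

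*Utilization.* A reader might extend the point to the observational win ratio and say that its interval treats patients as independent. The text does not support this. It puts site in the risk strata, names no variance method for that cohort's interval, and defers the adjustment method to the analysis plan. Nor is an interval from resampling 14 sites clearly better. In a check with a mean difference standing in for the win ratio, it rejected 4.5% to 6.1% of the time at a nominal 2.5%, and in most settings did worse than ignoring site.

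**Conclusion.** The point holds for the observational pain interference model only. The stated primary model is at odds with the protocol's own power section and with its handling of site for the other co-primary endpoint, and the choice of model is left open to the data.

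The size depends on assumptions that the documents do not settle. For between-site logit SDs of 1 to 2 in stent use and ICC 0.01 to 0.05, type I error is about 3% to 8% instead of 2.5%. If site outcome levels are unrelated to stenting rates and sites are of equal size, 14.7% is the upper bound at ICC 0.05. Correlation between the two adds bias and can push the error beyond that. Without between-site variation in stenting there is no inflation. Some variation is likely, because the urologist decides.

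The change should be made: it is cheap, and it brings the analysis into line with the plan's own reasoning.

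**What to change.** Pre-specify site in the primary observational pain interference model, whatever imbalance is seen. A fixed effect for site is preferable, and site already enters the utilization risk model in that form. A site random intercept together with the site's stent proportion as a covariate is an acceptable alternative. A plain random intercept is not enough, because it removes site confounding only in part. Delete the sentence that makes random effects conditional on further imbalance, and say in the analysis plan how surgeon clustering within site is handled.

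The cost is a wording change before data lock, with no new patients or data. The interval will be somewhat wider, and sites that stent nearly all or nearly none of their patients will contribute little to the estimate.
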